## Abstract

**Background:**

Reshaping the tumor microenvironment by novel immunotherapies represents a key strategy to improve cancer treatment. Nevertheless, responsiveness to these treatments is often correlated with the extent of T cell infiltration at the tumor site. Remarkably, microsatellite stable rectal cancer is characterized by poor T cell infiltration and, therefore, does not respond to immune checkpoint blockade. To date, the only available curative option for these patients relies on extensive surgery. With the aim to broaden the application of promising immunotherapies, it is necessary to develop alternative approaches to promote T cell infiltration into the tumor microenvironment of these tumors. In this regard, recent evidence shows that radiotherapy has profound immunostimulatory effects, hinting at the possibility of combining it with immunotherapy. The combination of long-course chemoradiotherapy and immune checkpoint inhibition was recently shown to be safe and yielded promising results in rectal cancer, however short-course radiotherapy and immune checkpoint inhibition have never been tested in these tumors.

**Methods:**

Our clinical trial investigates the clinical and biological impact of combining pembrolizumab with short-course radiotherapy in the neo-adjuvant treatment of localized rectal cancer. This phase II non-randomized study will recruit 25 patients who will receive short-course preoperative radiotherapy (5 Gy × 5 days) and four injections of pembrolizumab starting on the same day and on weeks 4, 7 and 10. Radical surgery will be performed three weeks after the last pembrolizumab injection. Our clinical trial includes an extensive translational research program involving the transcriptomic and proteomic analysis of tumor and blood samples throughout the course of the treatment.

**Discussion:**

Our study is the first clinical trial to combine short-course radiotherapy and immune checkpoint inhibition in rectal cancer, which could potentially result in a major breakthrough in the treatment of this cancer. Additionally, the translational research program will offer insights into immunological changes within the tumor and blood and their correlation with patient outcome. Taken together, our work will help optimizing future treatment combinations and, possibly, better selecting patients.

**Trial registration:**

This study was registered with www.clinicaltrial.gov: NCT04109755. Registration date: June, 2020.

## Background

Rectal cancer (RC) is one of the most frequently occurring cancers and leading cause of cancer death worldwide [1–3]. Apart from surgery, which has a massive impact on the quality of life of RC patients, management of RC largely relies on conventional methods such as chemotherapy (CT) and radiotherapy (RT). For tumors localized close to the anal margin or node positive tumors, which represent 45 to 60% of the newly diagnosed patients, European and American oncology guidelines recommend either five weeks of neoadjuvant chemo-RT (CRT) followed by an 8- to 12-week treatment-free interval before radical surgery, or a short-course preoperative RT (SCPRT) with surgery taking place either 1–2 or 8–10 weeks after RT [4, 5]. These two modalities of treatment are currently judged equivalent [6, 7].

The importance of an intact immune surveillance function in controlling tumor outgrowth has been known for decades [8]. In recent years, the field of cancer immunotherapy has seen considerable progress due to the discovery of new therapies targeting immune checkpoint molecules such as cytotoxic T lymphocyte-associated protein 4 (CTLA-4), programmed cell death 1 (PD1) and programmed cell death ligand 1 (PD-L1) [9]. Clinical trials investigating immune checkpoint inhibitors (ICIs) in advanced tumor settings have shown positive results in several cancers and these treatments have been integrated into standard of care [10, 11]. Although ICIs can provide deep and durable responses in some cancers, clinical benefit is usually limited to a subset of patients. In gastrointestinal cancers, impressive results have been obtained with the anti-PD1 antibody pembrolizumab in heavily pre-treated patients with advanced disease carrying mismatch repair deficient genes (dMMR) [12]. Tumors with dMMR are typically associated with microsatellite instability (MSI) and display a higher response rate to ICIs compared to microsatellite stable (MSS) tumors. Recently, Overman and colleagues published results of an anti-PD1 immunotherapy in second line treatment in MSI-H metastatic colorectal cancer (CRC) [13]. These early results showed 50% progression free survival (PFS) and 60% overall survival (OS) at two years, outperforming results obtained with second line chemotherapies [13]. Unfortunately, MSI-H tumors represent only 1 to 3% of RCs, and, consequently, the majority of RC patients will not respond to ICIs.

Accumulating evidence shows a correlation between tumor-infiltrating lymphocytes (TILs) and favorable prognosis in various malignancies [14]. In particular, the presence of CD8^+^ T cells and the ratio of CD8^+^ T cells/FoxP3^+^ regulatory T cells (Tregs) correlate with improved prognosis and long-term survival in solid malignancies [15]. As T cell infiltration is typically dictated by the presence of tumor-specific antigens (neoantigens), it is not surprising that MSI-H tumors display a greater number of TILs as compared to MSS cancers [16]. In line with these observations, high “immunoscores” were found predictive of response to ICIs [17, 18].

In order to broaden the application of ICIs to MSS RC, novel therapeutic approaches aiming at reconditioning the tumor microenvironment (TME) by either promoting TIL activation or infiltration are required. To this end, RT is a promising option, as recent evidence suggests that ionizing radiation can induce important immunomodulatory effects in the TME allowing trafficking of T cells into the tumor [19]. These studies speak in the favor of combining RT and ICIs. Lately, a bulk of work investigating the effect of radio-immunotherapy in pre-clinical tumor models of various solid cancers, including CRC, highlighted the potential benefit of this approach [20–22]. Following these results, a few clinical trials are evaluating the combination of RT and ICIs in RC (NCT02948348, NCT04124601, NCT04262687, NCT04558684), but always in combination with CT and in advanced clinical settings. Encouraging safety and toxicity profiles from these studies indicate that radio-immunotherapy combinations could represent a valid opportunity for RC patients. For instance, in the VOLTAGE trial (NCT02948348) where patients received CRT followed by the anti-PD1 antibody nivolumab, only mild toxicity was reported [23]. Moreover, 30% of patients with locally advanced MSS RC reached pathological complete response (pCR). Remarkably, our clinical trial represents the first study where the impact of combining the anti-PD1 antibody pembrolizumab with short-course RT in the neo-adjuvant treatment of localized RC will be evaluated (NCT04109755). Alongside this clinical trial, a translational research project will provide a deep understanding of the dynamic changes in the immune and tumor cell states that are associated with responses to treatment and patient outcome. Ultimately, these results will have profound implications for the treatment of RC patients and the design of future clinical trial protocols for other non-inflamed tumors.

## Method and design

### Hypothesis

We hypothesize that combining pembrolizumab with SCPRT can increase the histological response compared to the standard of care (RT alone) due to the increased immune infiltrate in the tumor (specifically CD8^+^ T cell and FOXP3^+^ T cell) in subjects with localized MSS and MSI RC.

### Objectives

The primary objective of this study is the assessment of the *pathological Complete Response (pCR)* after radio-immunotherapy. In addition to pCR rate, tumor regression grade (TRG) will be assessed as part of the diagnostic procedure for the evaluation of the response to treatment. Secondary objectives include *Tolerability and Safety*, *OS, DFS, Locoregional Relapse-Free Survival (LRRFS), Distant Metastasis-Free Survival (DMFS), Quality of Life, Post-Operative Complication* and *Quality of Surgery*. Lastly, this clinical trial comprises an exploratory objective that overlaps with a translational research program aiming at providing new insights into the tumor and immune cell states that are associated with response to treatment and identifying novel prognostic and predictive biomarkers for clinical decision making*.*

### Study endpoints: the clinical trial will assess the following parameters

*pCR by a complete histological assessment in conjunction with TRG* using the Mandard regression grade score. These parameters will be evaluated at the completion of the radio-immunotherapy treatment after the surgical procedure;*Tolerability and Safety* using the common terminology criteria for adverse events (CTCAE) Version 4.0 and Dindo Clavien classification of surgical complication. These parameters will be evaluated at the completion of the radio-immunotherapy treatment (i.e. proportion completing the planned neoadjuvant treatment and proportion proceeding to surgery);*OS*, defined as the time from study entry until death due to any cause. Subjects who have not died at the time of last known follow-up will be censored;*DFS,* defined as the time from study entry until recurrence, second primary cancer, or death without evidence of recurrence or second primary cancer;*LRRFS*, defined as the time from surgery until local or regional recurrence. LRRFS is evaluated in patients who had an R0 resection only;*DMFS*, defined as the time from surgery to metastatic recurrence;*Quality of Life* using EORTC QLQ-C30 questionnaire and EORTC QLQ-CR29;*Post-Operative Complication* according to the Dindo-Clavien score;*Quality of Surgery* according to Nagtegaal’s recommendations;*Tumor Immunome* and *Peripheral Immune Responses* in relation to the clinical outcomes.Comparison of the tumor immune microenviroment before (treatment-naïve) and after neo-adjuvant radio-immunotherapy using RNA sequencing and flow cytometry.Quantitative and qualitative assessment of the immune responses in the periphery by analysis of peripheral blood (peripheral blood mononuclear cells (PBMC), circulating tumor DNA (ctDNA), serum and plasma).Correlation of these findings with clinicopathological parameters and clinical outcomes.

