### Study design

This trial is a phase II, single arm study, including 25 patients with localized RC. Following diagnosis and workout, patients will receive SCPRT (5 Gy × 5 days) and four injections of pembrolizumab, on weeks 1, 4, 7 and 10. This phase of treatment will last 12 weeks, then surgery will be performed. Immune response will be monitored in the blood (specifically in PBMC) before, during radio-immunotherapy and after surgery and within the tumor before and after treatment. An outline of the study design is depicted in Fig. 1.

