### Statistical analysis

The primary outcome of this study is pCR. The pCR rate, defined as the absence of residual invasive disease in the rectum and in the lymph nodes at the completion of the neoadjuvant treatment [24], reaches 12–16% in patients receiving treated with SCPRT with delayed surgery or CRT, respectively [5]. Remarkably, induction CT before CRT and surgery increase pCR to 30%-35% [25]. Our hypothesis is that the our sttudy intervention results in a pCR rate that is superior to that of SCPRT. The null hypothesis assumes a 10% pCR rate, and the alternative a 30% pCR rate, which at the usual alpha (0.05) and beta (0.2) cutoffs, require a population of 25 patients, using an exact binomial sample size calculation. The null hypothesis will be rejected if at least 6 patients out of 25 meet the primary endpoint.

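### DFS starts at study entry but has no event for a tumour that is never cleared, so such a patient counts as disease-free until death or a second primary

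*Protocol article*

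**What the plan says.** All the definitions stand in the Study endpoints section of the protocol article.

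- DFS is "defined as the time from study entry until recurrence, second primary cancer, or death without evidence of recurrence or second primary cancer".
- LRRFS is "defined as the time from surgery until local or regional recurrence", and "LRRFS is evaluated in patients who had an R0 resection only".
- DMFS is "defined as the time from surgery to metastatic recurrence". It carries no R0 condition.
- OS is "defined as the time from study entry until death due to any cause".

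The same section foresees that some patients may not reach surgery. It lists the "proportion completing the planned neoadjuvant treatment and proportion proceeding to surgery", but only under tolerability and safety.

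On timing, the Study design section says "This phase of treatment will last 12 weeks, then surgery will be performed". Table 1 puts surgery at day 85 with an allowance of 28 further days. Table 1 also has discontinuation columns, with an assessment at the event and then every 12 weeks.

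**The concern.** The starting point and the event list of DFS do not match. The events are those of a cohort already rendered tumour-free by surgery. The clock, however, starts before any treatment, in patients who all have an untreated rectal tumour. The only non-fatal event tied to that tumour is recurrence, which presupposes that it was first removed.

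The patients who fall through are those in whom neoadjuvant treatment and surgery never achieved clearance. They would be carried as disease-free for as long as they live without a second primary. That makes the DFS estimate too favourable.

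It could also mislead the translational work, which relates immune findings to clinical outcomes. A patient whose cancer spreads during treatment is an informative non-responder, yet would carry a favourable DFS status.

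**Working it through.** **1. The plan's own figure.** The article gives no design figure for DFS, LRRFS or DMFS. Its only design figure is for pCR: "The null hypothesis assumes a 10% pCR rate, and the alternative a 30% pCR rate", with 25 patients and rejection at 6 or more. The exact binomial reproduces it:

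- P(X ≥ 6 | n = 25, p = 0.10) = 0.0334
- P(X ≥ 6 | n = 25, p = 0.30) = 0.8065

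Twenty-five is the smallest n with one-sided alpha at most 0.05 and power at least 0.80. The present point does not touch this.

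**2. Time before surgery.** From Table 1, (85 − 1)/7 = 12 weeks and (85 + 28 − 1)/7 = 16 weeks after day 1. The DFS clock runs through these 12 to 16 weeks with no event available for the index tumour except death.

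**3. Patient types set against the definitions.**

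| Patient | DFS | LRRFS | DMFS |
|---|---|---|---|
| Metastasis before surgery, not operated | no event until death or second primary | outside the set | no time zero |
| Progression precluding curative resection, not operated | no event until death or second primary | outside the set | no time zero |
| Metastasis found at surgery | not a recurrence, so no event for it | in the set only if R0 | in the set, but the metastasis is already there at time zero |
| R2 resection | no event for the residual tumour | outside the set | in the set; later metastasis can count |
| Local progression, then R0 resection | cleared; not a failure | in the set | in the set |

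The first four rows are the problem. The last is not. OS picks up the first four only at death.

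**4. Size.** Let e be the number of patients with a DFS event by the landmark under the stated definition. Let k be the number of never-cleared patients who are alive then without a second primary. With all 25 followed to the landmark:

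- stated DFS = 1 − e/25
- DFS counting the failures = 1 − (e + k)/25
- difference = k/25

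The documents give no value for k. For an assumed k of 0, 1, 2 and 3, the difference is 0, 4, 8 and 12 percentage points. The difference does not depend on e.

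**5. Illustration.** Assume that 25% of the other 25 − k patients have a counted event by 3 years, so e = 0.25 × (25 − k). This rate is not in the documents.

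| k | e | Stated DFS | DFS counting the k failures |
|---|---|---|---|
| 0 | 6.25 | 75% | 75% |
| 1 | 6.00 | 76% | 72% |
| 2 | 5.75 | 77% | 69% |
| 3 | 5.50 | 78% | 66% |

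In this example stated DFS rises as early failures become more common, which is the wrong direction for an efficacy endpoint.

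**6. Chance that it arises.** With an assumed risk q per patient, the chance of at least one such failure in 25 is 1 − (1 − q)^25. This is 64% at q = 4% and 96% at q = 12%. These risks are also assumptions.

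**The case against.** **Condensed text.** The definitions are one-line summaries in an article, and event derivation may be spelled out in a full protocol or SAP that is not shown. The sponsor may also mean recurrence to include progression before surgery. But this is not a case of missing detail. The article states an event list and an origin, and applied as written they misclassify these patients. The two readings give different DFS estimates, so the wording needs settling.

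**Size and rank.** DFS is a secondary endpoint. The exact 95% interval around, say, 20/25 runs from about 59% to 93%, so a shift of 4 to 12 points lies within sampling error. That supports a modest ranking. It does not excuse the shift, which always goes in the favourable direction. Affected patients who die before the landmark already count as DFS events, so the gap shrinks and can be zero.

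**Visibility.** The proportion reaching surgery is reported and OS counts all deaths, so the losses are not wholly hidden. That is true, but neither records a never-cleared tumour when it is found.

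**Stronger readings that the text does not support.**

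- A reader might infer that DFS counts only recurrence. It also counts second primary cancer and death.
- A reader might infer that DMFS loses the same patients as LRRFS. It has no R0 condition, so operated R1 and R2 patients stay in it; only unoperated patients drop out.
- A reader might treat LRRFS as defective. Measuring it from surgery in R0 patients is a coherent conditional endpoint, stated openly. Replacing it would be a preference.
- A reader might count every local progression before surgery as a failure. A patient who then has an R0 resection has been cleared.
- A reader might infer an unfair comparison with historical DFS. The article gives no historical DFS, LRRFS or DMFS figure; its historical comparisons concern pCR and tumour regression.

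**Conclusion.** The point holds for the DFS event list. DFS as defined cannot register metastasis found before or at surgery, progression that prevents curative resection, or residual tumour after R2 resection. LRRFS and DMFS do not make up for this, because of their population and time origin.

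The overstatement is up to 4 percentage points per affected patient, or 0 to 12 points for an assumed 0 to 3 patients. This rests on three assumptions: complete follow-up to the landmark, affected patients alive then without a second primary, and recurrence read in its plain sense. With earlier censoring, a patient's weight in a Kaplan–Meier estimate need not be exactly 1/25. No rate of such failures stands in the article, so none of these figures is a forecast.

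This should be corrected, but it concerns secondary endpoints only. The pCR sample size and decision rule stand.

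**What to change.** - Keep study entry as the DFS origin. Add as events, each dated when found: metastasis detected before or at surgery; progression that precludes curative resection; and R2 resection or non-resection because of tumour. Non-resection for other reasons without progression, such as a patient declining surgery, should not count as a disease event.
- State how R1 resection is counted, and apply the same rule in every endpoint. Otherwise one patient could be a locoregional failure and disease-free at once.
- Alternatively, rename the endpoint event-free survival with this event list.
- Report distant metastasis from study entry in all enrolled patients alongside DMFS.
- Keep LRRFS, label it as conditional on R0 resection, and give its denominator.

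The cost is protocol and SAP wording and a small change in event derivation. DFS becomes slightly less favourable. Dating failures before surgery depends on when patients are restaged. Table 1 as shown lists no restaging, so the sponsor should confirm that the full protocol already collects those dates.

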### Study design

This trial is a phase II, single arm study, including 25 patients with localized RC. Following diagnosis and workout, patients will receive SCPRT (5 Gy × 5 days) and four injections of pembrolizumab, on weeks 1, 4, 7 and 10. This phase of treatment will last 12 weeks, then surgery will be performed. Immune response will be monitored in the blood (specifically in PBMC) before, during radio-immunotherapy and after surgery and within the tumor before and after treatment. An outline of the study design is depicted in Fig. 1.

**Fig.1 Fig1:**
[figure not shown]
Flowchart of the study. RC: rectal cancer, MSS: microsatellite stable, ECOG: Eastern Co-operative Oncology Group, EUS: endoscopy ultrasound, MRI: magnetic resonance imaging, CT: computed tomography

### Study population

#### Inclusion criteria

Participants are eligible to be included in the study only if all of the following criteria apply:Male/female participants must be at least 18 years old, have adequate health conditions and be willing to comply with the study protocol.Participants must have been diagnosed with localized RC and not being treated for this disease before the start of the clinical trial:cT3a/b very low, levators clear, mesorectal fascia clear or cT3a/b in mid- or high rectum, cT1,2,3 and cN1-2 (not extranodal), no extramural vascular invasion;cT3c/d or very low localisation levators threatened, mesorectal fascia clear;cT3c/d mid-rectum, cT1,2,3 and cN1–N2 (extranodal), extramural vascular invasion present, limited cT4aN0.A multi-disciplinary tumor board should recommend neo-adjuvant SCPRT and surgery as the optimal treatment option for these patients.

#### Exclusion criteria

Participants are excluded from the study if any of the following criteria apply:Participants who have received anti-cancer therapy, live vaccine or have participated in other investigational trials in close proximity with the start of the clinical trial. If treated with RT, received major surgery or particpated in another study, the participant has to be fully recovered.Participant suffering from active autoimmune diseases, infections, immunodeficiency, other malignancies or health conditions that could confound the results of the study and/or interfere with the subject’s participation for the full duration of the study.

### Study interventions: the clinical trial will include the following therapeutic interventions

#### Biopsy

A treatment-naïve biopsy will be collected within a week before the start of the trial.

#### Pembrolizumab

Four injections of pembrolizumab will be administrated intravenously (IV) at a fixed dose of 200mg, over a period of 9 weeks, starting on the first day of the SCPRT and repeated every three weeks. There is no maintenance treatment.

#### External beam radiotherapy

SCPRT will be administered using volumetric-modulated arc therapy (VMAT) to a prescription dose of 25 Gy in 5 fractions of 5 Gy to the planning target volume (PTV) over 5 days (Monday to Friday). RT starts on day 1 of treatment (always on a Monday).

#### Surgery

Surgical procedure will take place 12 weeks after the end of the RT, meaning three weeks after the last (fourth) injection of pembrolizumab.

